### **21.3 Objection by minors or incapacitated subjects (if applicable)**

The children can withdraw from the study at any time, without penalty or impact on treatment. (art 4 lid 2 WMO) Neither will the child be forced to undergo the additional tests, such as muscle strength testing, the ultrasound evaluation of the skeletal muscle and adipose tissue compartments, or the questionnaires and follow-up evaluations. In this matter, also non-verbal resistance will be taken into account by the investigator's team. The specific test will then not be performed, without taking the subject out of the study as a whole.

#### **21.4 Benefits and risks assessment, group relatedness**

During the informed consent process, it will be made extremely clear that participation in this study will provide no direct benefits to the patient and that refusal to participate will have zero impact on the care received by any of the nursing medical staff. The risks will be kept to a minimum. This study requires this specific study group of critically ill children of different age groups. Although the study has been performed in adults, these results should not be translated directly to children as both the metabolic as well as nutritional kinetics in children of different age groups vary significantly from adults.

#### **21.5 Compensation for injury**

The sponsor/investigator has a liability insurance which is in accordance with article 7, subsection 6 of the WMO.

No fault insurance is covered by Fortis Corporate Insurance NV (Leuven) and Akkermans Van Elten Assurantiën BV (Rotterdam).

The sponsor has an insurance which is in accordance with the legal requirements in the Netherlands (Article 7 WMO and the Measure regarding Compulsory Insurance for Clinical Research in Humans of 23th June 2003). This insurance provides cover for damage to research subjects through injury or death caused by the study.

4. € 450.000,-- (i.e. four hundred and fifty thousand Euro) for death or injury for each subject who participates in the Research;
5. € 3.500.000,-- (i.e. three million five hundred thousand Euro) for death or injury for all subjects who participate in the Research;
6. € 5.000.000,-- (i.e. five million Euro) for the total damage incurred by the organisation for all damage disclosed by scientific research for the Sponsor as 'verrichter' in the meaning of said Act in each year of insurance coverage.

The insurance applies to the damage that becomes apparent during the study or within 4 years after the end of the study.

#### **21.6 Incentives**

Not applicable

## **22. ADMINISTRATIVE ASPECTS AND PUBLICATION**

### **22.1 Handling and storage of data and documents**

Data are collected electronically in a pseudonymized CRF, unambiguously linked to the source file. The subject identification codes are safeguarded by the principle investigators. Data are manually transferred (and checked for accuracy) into the CRF by the clinical research assistance team on a daily basis from the ICU PDMS and the Leuven University Hospitals Clinical Working Station (KWS). Extensive range and consistency checks are performed by the study monitor. Vital status at 90 days will be recorded for all patients, by the National Death Registries when this information is not available in the hospital information system or the regional network of pediatricians.

The handling of personal data will comply with the Dutch Personal Data Protection Act (in Dutch: De Wet Bescherming Persoonsgegevens, WBP).

### **22.2 Amendments**

Amendments are changes made to the research after a favourable opinion by the accredited METC has been given. All amendments will be notified to the METC that gave a favourable opinion.

All substantial amendments will be notified to the METC and to the competent authority.

Non-substantial amendments will not be notified to the accredited METC and the competent authority, but will be recorded and filed by the sponsor.

### **22.3 Annual progress report**

The sponsor/investigator will submit a summary of the progress of the trial to the accredited METC once a year. Information will be provided on the date of inclusion of the first subject, numbers of subjects included and numbers of subjects that have completed the trial, serious adverse events/ serious adverse reactions, other problems, and amendments.

### **22.4 End of study report**

The investigator will notify the accredited METC of the end of the study within a period of 8 weeks. The end of the study is defined the time-point 90 days after the inclusion of the last patient.

In case the study is ended prematurely, the investigator will notify the accredited METC, including the reasons for the premature termination.

Within one year after the end of the study, the investigator/sponsor will submit a final study report with the results of the study, including any publications/abstracts of the study, to the accredited METC.

### **22.5 Public disclosure and publication policy**

This is an investigator initiated study. This study will be registered as a clinical trial in a public trial registry.

The investigators aim to publish all results obtained from the study unreservedly.

## **Summary of changes in protocol PEPaNIC**

## PEPaNIC protocol amendment 1, Date May 2, 2013

Addition of:

1. Stollery Children's Hospital Edmonton as recruiting site
2. Collecting buccal swabs as reflection of intestinal intolerance and inflammation

- Ad 1: introduction and rationale (page 10)

*One of the goals of the PEPaNIC study is to look into the tolerance for enteral nutrition (EN). In critically ill children EN is preferred because it is more physiological, presents fewer complications, leads to a better outcome and is less expensive than PN. However, EN often fails in this patient group due to impaired gastrointestinal (GI) motility, digestion and absorption following ischemia, inflammation or starvation leading to intolerance to EN. To improve future EN tolerance in critically ill children we have to gain insight in parameters of influence in this complex process.*

*One of the parameters is mucosal inflammation, which can be related to malabsorption, as seen in patients with inflammatory bowel disease (IBD). Intestinal epithelial cells play a role in initiating and regulating mucosal immune responses through the secretion of chemokines. Studies in patients with IBD showed that epithelial cells derived from the intestine produce significant amounts of pro and anti-inflammatory chemokines (CXCL-8, CXCL-9 and CXCL-10). Chemokine expression can be measured in buccal epithelium which can be used as a reflection of intestinal inflammation.*

- Ad 2: objectives (page 13):  
*To study the underlying physiological mechanisms of enteral nutrition (EN) intolerance of critically ill children and to identify markers of tolerance for EN to use in future intervention studies clinical signs of intolerance (gastric residual volume, diarrhoea, vomiting, abdominal swelling) will be recorded. Buccal swabs will be collected at several moments and will be stored for analysis (epithelial cell expression of chemokines).*
- Ad 5.1: treatment of subjects - investigational treatment (page 21): In **Edmonton** patients in all age groups receive continuous insulin infusion to target blood glucose levels <180 mg/dl
- Ad 7.1.2: methods – secondary study parameters/endpoints(page 26):  
*h. Enteral nutrition (EN) tolerance: proportion of patients with diarrhoea, high gastric residual volumes, vomiting and/or abdominal swelling and relation with buccal epithelial cell expression of chemokines (CXCL-8, CXCL-9 and CXCL-10)*
- Ad 7.3: data collection following recruitment (page 33-34):

*Buccal swabs will be collected at day of admission (day 1), day 2, 4 and 6, and possibly on day of discharge and will be immersed in RNA-later and stored at -80C. Buccal epithelial cell expression of chemokines (CXCL-8, CXCL-9 and CXCL-10) will be measured in by Taqman analysis.*

- *In children > 10 kg 1,8 milliliter extra blood (EDTA and heparine) will be collected on 4 selected days*

Informed consents were adapted accordingly.

[figure not shown]

CENTRALE  
COMMISSIE  
MENSgebonden  
ONDERZOEK

Erasmus MC –Sophia afdeling Intensive Care kindergeneeskunde  
Tav [name], [name]  
[name]  
[name]

12 juni 2013  
uw kenmerk: n.v.t., ons kenmerk: CCMO13.0467/GK/cb/38772

## PEPaNIC protocol amendment 2, Date December, 17, 2013

Addition of:

1. Collecting hair samples for studying cortisol metabolism levels
2. collecting blood samples for studying epigenetic changes

- Ad 7.1.2: methods – secondary study parameters/endpoints(page 30):

*Impact of early versus late PN on the neuroendocrine axes: The metabolism of cortisol will be studied further by the relative levels of its metabolites excreted in urine (26) and by collecting hair samples for the long term cortisol levels.*

- Ad 7.3: data collection following recruitment (page 33):

*Around 100 strands of hair from the posterior vertex of the scalp will be cut off as soon as possible after admission and this will be repeated after 3 weeks- 2 months if possible.*

- Ad 7.3: data collection following recruitment (page 34):

*On day 3,5 and 7 a 'PAX-tube' (containing 2 milliliter blood) will be collected.*

Informed consents were adapted accordingly.

Erasmus MC  
afdeling IC kinderen  
[name]  
[name]  
[name]

[figure not shown]

Centrale  
Commissie  
Mensgebonden  
Onderzoek

Ons kenmerk: CCMO14.0023/GK/cb/38772

Uw kenmerk: nvt

Datum: 10 januari 2014

Betreft: Nader besluit amendement NL38772

Postadres:

[name]

[name]

Bezoekadres:

[name]

[name]

t. [name]

[contact]

www.ccmo.nl

geachte heer [name],

Hierbij zend ik u het besluit van de CCMO inzake het amendement bij het onderzoek 'Pediatric Early versus late Parenteral Nutrition in Critical Illness', (NL38772.000.12).

De CCMO verleent goedkeuring aan genoemd amendement. Voor de overwegingen hierbij verwijs ik u naar het bijgevoegde besluit.

Wij verzoeken u alle bij de uitvoering van het onderzoek betrokken partijen van het besluit op de hoogte te brengen. U kunt hiervoor gebruikmaken van de digitale versie van het besluit dat in ToetsingOnline is te vinden in het dossier van deze studie.

Ik hoop u hiermee naar behoren te hebben geïnformeerd.

Met vriendelijke groet,  
Namens de Centrale Commissie Mensgebonden Onderzoek

[figure not shown]  
Prof dr [name], voorzitter

## **Final statistical analysis plan**

*NB: only one version of the SAP was created and therefore no  
summary of changes has been included*

## **Background**

The prevalence of undernutrition in children who are admitted to the Pediatric Intensive Care Unit (PICU) is up to 24%. Undernutrition on admission is associated with increased mortality and morbidity such as infectious complications, longer need for mechanical ventilation and prolonged hospital stay.

Hulst et al showed that the nutritional status of children admitted to the PICU declined from admission to discharge from the PICU and that these children showed catch-up growth within 6 months. Both protein intake of at least 2.3 mg/kg/day during PICU stay and higher enteral caloric intake after PICU stay have been associated with an increase in weight-for-age (WFA) SD score in subgroups of children. However, this association could not be found for duration of parenteral nutrition (PN). Furthermore, it is unknown if deterioration of nutritional status during PICU stay independently impairs clinical outcome.

The PEPaNIC trial in 1440 critically ill children showed that withholding PN for one week resulted in fewer new infections and reduced the duration of PICU stay as compared with early initiation of PN. These clinical benefits were even larger in children who were at high risk of undernutrition as reflected by a high score on the Screening Tool for Risk on Nutritional status and Growth (STRONGkids). However, the STRONGkids score has originally been developed for children admitted to the pediatric ward, not children admitted to the PICU. The effect of late initiation of PN in children who were undernourished upon admission has not yet been evaluated.

## **Aims and hypotheses**

The aim of this secondary analysis is to investigate the clinical effect of late PN in children who were undernourished upon admission, and to investigate the prognostic value of change in weight during PICU stay and the effect of late PN hereon. Furthermore, we will analyze the impact of Late PN on the relation between weight change and clinical outcome in relation to undernourishment upon admission, if the number of patients in each group is sufficiently large.

We hypothesize that undernourished children who have been allocated to the late PN group will have less new infections and a shorter duration of PICU stay than those allocated to the early PN group. Furthermore, in line with previous findings, we expect that weight deterioration is associated with worse clinical outcome. We expect that there is no difference in weight change between children receiving early PN and those receiving late PN, and that the relation between weight change and clinical outcome is not affected by late PN.

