#### *Outcomes*

Primary outcomes are incidence of new infections and duration of PICU dependency, which will be reported as the crude number of PICU days and as the time to live discharge from the PICU, to account for mortality as a competing risk.

Secondary outcomes are duration of mechanical ventilation (and time to life weaning from mechanical ventilation), duration of hospital stay (and time to life discharge from the hospital), and the safety outcomes 7-day mortality (i.e. during the intervention period), 90-day mortality and hypoglycemia during the first week.

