#### *Statistical analyses*

As the sample size of the present study depended on the number of undernourished children included in the PEPaNIC-trial, we plan to perform a retrospective power analysis based on observed differences for risk of new infection as primary endpoint, rather than performing an a priori sample size calculation.

Variables will be reported as percentages, means ( $\pm$ SD) if normally distributed or as medians (IQR) if not-normally distributed. Change in weight will be reported as change in WFA or BFA SD score. Proportions will be analyzed univariably using chi-square test, means with t-test and medians with Mann Whitney test. The time-to-event effect sizes will be estimated with use of Cox proportional-hazard analysis, with data censored at 90 days. To take into account death as a competing risk for outcomes related to duration of care, data for non-survivors will be censored at 91 days. These time-to-event outcomes will be analyzed adjusted for baseline risk factors treatment center, age, diagnosis group, STRONGkids category, PIM2 score and PELOD score. The multivariable analysis of the effect of the intervention on dichotomized outcomes, adjusted for baseline risk factors, will be performed using logistic regression. Analyses regarding change in weight will additionally be adjusted for malnourishment upon admission.

P-values  $\leq 0.05$  will be considered statistically significant. P-values for interaction were calculated with the use of multivariable logistic regression analyses and multivariable Cox proportional-hazard analyses with a threshold for significance of interaction set at  $P \leq 0.10$ .

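### The SAP's prognostic analysis of weight change over the PICU stay can confirm its hypothesis through length of stay alone; it needs a landmark or time-dependent weight.

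*Supplement*

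**What the plan says.** The SAP (Aims and hypotheses) sets out "to investigate the prognostic value of change in weight during PICU stay and the effect of late PN hereon" and expects weight deterioration to go with worse clinical outcome. Under Outcomes: "Primary outcomes are incidence of new infections and duration of PICU dependency". The second is reported as crude PICU days and as time to live discharge.

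Under Statistical analyses, "Change in weight will be reported as change in WFA or BFA SD score", with no division by elapsed time. For the models: "The time-to-event effect sizes will be estimated with use of Cox proportional-hazard analysis, with data censored at 90 days", with non-survivors placed at 91 days and logistic regression for dichotomous outcomes. The adjustment set is centre, age, diagnosis group, STRONGkids category, PIM2 and PELOD. For this aim one item is added: "Analyses regarding change in weight will additionally be adjusted for malnourishment upon admission".

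Data collection and definitions limits the weight-change analyses to the Dutch patients, because repeat measurements were not made in Belgium and Canada. Neither the SAP nor the final protocol (section 18.3, Additional data collection) gives the days of weighing during the PICU stay. No landmark, fixed window, per-day rate, time-dependent covariate or adjustment for days between weighings is named.

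**The concern.** A predictor should be known before the outcome it predicts. Change over the PICU stay is known only when the child leaves, and leaving is the outcome. Two routes then produce an association with no prognostic content. A child who stays longer has more days in which to lose weight. A child who acquires an infection may lose weight because of it, and the loss is then counted as a predictor of that infection. Baseline covariates remove only the part of stay that they predict.

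The SAP's Background supplies the mechanism: it cites a study in which nutritional status declined between PICU admission and discharge. It also notes that it is unknown whether such deterioration independently impairs outcome. The planned model cannot answer that, because its result would look much the same if weight loss were only a marker of time spent in the unit. At stake is a finding that matches the stated hypothesis whether or not that hypothesis is true.

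**Working it through.** **Plan's own figure.** The SAP gives none for the weight-change analyses, so there is nothing to reproduce on this point.

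**Model under no prognostic effect.** For a stay of L days, weight change is w = −r·L + e, where r is the daily loss in SD score and e is noise with mean 0 and SD s. Weight affects neither discharge nor infection.

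**Inputs.**
- From the documents: mean stay 7.8 and median 2 days in Rotterdam (final protocol 15.1, all 2010 admissions). For a log-normal stay, log-SD = √(2·ln(7.8/2)) = 1.65. A narrower stay (log-SD 1.1, same mean) was also run. Late PN was given a stay 1 day shorter, the reduction planned for in 15.4.
- Assumed: r = 0 to 0.05 SD per day, s = 0.5, N = 300 or 700 Dutch children, infection hazard 0.028 per day.

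**Hand check.** With log-SD 1.1, the SD of stay is 7.8·√(exp(1.21) − 1) ≈ 12.0 days, before the simulation's cap at 90 days. With r = 0.01, r·SD = 0.12. The correlation of w with stay is −0.12/√(0.12² + 0.5²) ≈ −0.23. At N = 300 its standard error is about 1/√300 = 0.058, so it is some four standard errors from zero.

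**Simulation.** There were 200 runs per cell. Discharge was analysed by a Cox model on w and arm. Infection was analysed by a t-test of w by infection status. The day-4 landmark used change to day 4 in children still in PICU, with discharge counted from day 4. Ranges run over both N and both stay distributions.

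| Loss per day (SD) | HR for live discharge per 0.5 SD better change | p ≤ 0.05, discharge | p ≤ 0.05, infection | Day-4 landmark HR | p ≤ 0.05, landmark |
|---|---|---|---|---|---|
| 0 | 1.00 | 4–5.5% | 4–5.5% | 0.995–1.011 | 3.5–5% |
| 0.01 | 1.20–1.25 | 88–100% | 25–93.5% | 0.997–1.015 | 5–9% |
| 0.02 | 1.37–1.43 | 100% | 74.5–100% | 0.991–1.006 | 4–7% |
| 0.05 | 1.68–1.70 | 100% | 99.5–100% | 0.989–0.999 | 3.5–6% |

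The Monte Carlo standard error at 5% is √(0.05·0.95/200) ≈ 1.5 points. The landmark rates average 5.2% over the 16 cells.

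**Second set of assumptions.** Median stay 4.5 days, noise SD 0.3, infection hazard 0.03 per day, N = 300, losses of 0.01, 0.02 and 0.03 SD per day:
- Discharge HR per 0.5 SD lost: 0.72, 0.55 and 0.44, significant in 95%, 100% and 100% of runs.
- Infection odds ratio: 1.35, 1.81 and 2.14, significant in 20%, 70% and 91% of runs.
- With N = 150, the discharge analysis is significant in 71%, 99.5% and 100% of runs.

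**Arm comparison of weight change, no per-day arm difference.** The expected shift is about r × 1 day. Simulated shifts were 0.007 to 0.056 SD, with p ≤ 0.05 in 3.5–14% of runs against a nominal 5%.

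**The case against.** **Specification.** The SAP does not say how weight change enters a model or on which days children were weighed. A fixed covariate over the whole stay is an inference, so this is a gap in specification rather than a documented choice. That stands. However, the aim's wording points to the whole stay, and no listed method would prevent the problem.

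**Outcomes beyond the PICU stay.** The SAP also lists hospital stay and "the safety outcomes 7-day mortality (i.e. during the intervention period), 90-day mortality and hypoglycemia during the first week". Hospital stay and 90-day mortality reach past PICU discharge, so the problem is not uniform. Hospital stay still contains the PICU stay. Both primary outcomes are fully exposed.

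**Assumption-driven size.** This stands. Daily loss, noise and the Dutch N are in no document, the Rotterdam stay figures are not those of the trial population, and the simulations omit the SAP's baseline covariates. The direction of the bias is firmer than its size.

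**Stronger readings that a reader might infer.**
- That length of stay invalidates the late-PN effect on weight change. The documents do not support this. The arms were randomised, so stay is a consequence of treatment and not a confounder. The total effect is a valid contrast, although it mixes daily loss with fewer days, since the Background reports that "withholding PN for one week resulted in fewer new infections and reduced the duration of PICU stay".
- That quickly discharged children lack a second weight. No section says so.
- That a non-significant result will be read as equivalence. The SAP says "We expect that there is no difference in weight change between children receiving early PN and those receiving late PN" and gives a significance threshold, but does not state that inference.
- That the whole SAP is affected. The aim on children undernourished at admission uses a baseline subgroup and is untouched.

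**Conclusion.** The concern holds for the prognostic analysis of weight change against new infections and time to live PICU discharge. If nutritional status falls with each day in the unit, the planned models will usually report that weight loss goes with worse outcome even when it carries no prognostic information. With 300 to 700 children and a loss of 0.01 to 0.03 SD per day, false positives are about 90–100% for discharge and about 20–100% for infection. The apparent discharge HR per 0.5 SD lost is roughly 0.83 (1/1.20) to 0.44 across the assumptions tried. With no daily loss, error is nominal, so the result depends on accrual over the stay. The weight-change hypothesis cannot be interpreted as planned. The randomised arm comparison of total weight change stands.

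**What to change.** 1. State the days on which the Dutch children were weighed and which weights define the change.
2. For infections and PICU discharge, replace the whole-stay predictor. Either use a landmark (change from admission to an early fixed day such as day 4, children still in PICU, only later events counted), or enter the latest weight as a time-dependent Cox covariate. For infection, the second option means analysing time to first new infection rather than a logistic model.
3. Adjust for the continuous admission SD score, which the SAP already computes, in place of the yes/no malnourishment flag. This improves the adjustment but does not cure the timing problem.
4. Keep the arm comparison of total change. Supplement it with change to a fixed day or per day, and report by arm how many children have no second weight.

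**Cost.** SAP wording and some reanalysis of existing Dutch repeat weights; their number and timing must be checked first. The landmark set is smaller. If the 15.1 stay figures applied (log-normal, median 2, log-SD 1.65), the share still in PICU would be P(Z > ln(4/2)/1.65) ≈ 34% after day 4 and P(Z > ln(7/2)/1.65) ≈ 22% after day 7. Trial children, selected for an expected stay above 24 hours, may stay longer. An early landmark or the time-dependent model is therefore preferable to day 7.

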## **Methods**

### *Context*

These hypotheses will be tested with data from the PEPaNIC trial. A total of 1440 children from three large tertiary referral PICUs in three different countries (KU Leuven in Belgium, Erasmus MC in The Netherlands and Stollery Children's Hospital in Canada) were randomly assigned to late PN (Late PN; intervention) or early PN (Early PN; standard care). Initiation and incline of enteral nutrition and administration of trace elements, minerals and vitamins were identical in both groups. Patients assigned to the late PN group (n=717) received no PN at all during the first week of critical illness. Patients in the early PN group (n=723) received PN within 24 hours after admission to supplement insufficient enteral nutrition. After the first week,

PN was administered equally in both groups according to standard nutritional protocol if enteral nutrition was insufficient to meet nutritional goals. The full study protocol and clinical outcomes have been reported in detail elsewhere.

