#### *Data collection and definitions*

Data on patient characteristics, outcome measurements and parameters for nutritional status were prospectively collected and registered in the study database. Since multiple measurements of weight and height were not performed for the Belgian and Canadian patients, we will exclude these patients for the analyses concerning change in weight during PICU stay.

The nutritional status will be defined based on WFA in children younger than one year and BMI-for-age (BFA) in children older than one year. Acute undernutrition is defined as WFA or BFA SD scores  $<-2$ . Country specific reference values for WFA and BFA will be used to calculate SD scores, if possible. If these are unavailable, WHO reference values will be used.

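### Two SAP hypotheses are of no effect (weight change, and its relation to outcome), yet the only criteria are difference and interaction p-values in the Dutch children, and a non-significant result cannot support either

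*Supplement*

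**What the plan says.** The SAP's Aims and hypotheses section contains two expectations of no effect. The first is "We expect that there is no difference in weight change between children receiving early PN and those receiving late PN". The second is that "the relation between weight change and clinical outcome is not affected by late PN". The Context section that follows begins "These hypotheses will be tested with data from the PEPaNIC trial", so both are put forward for testing.

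The Data collection and definitions section restricts the population. Repeated weights and heights were not taken in the Belgian and Canadian children, so "we will exclude these patients for the analyses concerning change in weight during PICU stay". Of the three centres, that leaves "Erasmus MC in The Netherlands". The number of Dutch children with two weights is not given.

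The Statistical analyses section sets the scale and the tests:

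- **Scale:** "Change in weight will be reported as change in WFA or BFA SD score".
- **Group comparisons:** "means with t-test and medians with Mann Whitney test", with significance at P≤0.05.
- **Interactions:** logistic models and "multivariable Cox proportional-hazard analyses with a threshold for significance of interaction set at" P≤0.10. The arm-by-weight-change term is not named explicitly.

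There is no equivalence margin, no rule based on a confidence interval, and no power figure for weight change. The one planned power analysis is retrospective and concerns new infections.

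**The concern.** A difference test takes no difference as its null, and an interaction test takes no interaction as its null. Here those nulls are the SAP's own hypotheses. The plan can therefore contradict them by rejecting, but it has no way of supporting them, because failing to reject says nothing about how large an effect the data still allow.

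Two clinical questions are at stake: whether withholding PN costs children weight, and whether weight loss matters more when PN is withheld. A p-value above the threshold, from one centre's children, could be taken as reassurance on both without any bound having been shown. The risk is greater for the interaction, because such a test needs far more data than a comparison of means.

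**Working it through.** **The documents' only power figure.** Protocol section 15.4 plans for infections of 20% versus 15% with 720 per arm, and gives power of 80% one-tailed and 70% two-tailed. With the usual two-proportion formula:

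- SE under the null = √(2×0.175×0.825/720) = 0.02003
- SE under the alternative = √((0.16+0.1275)/720) = 0.01998
- One-tailed: (0.05 − 1.645×0.02003)/0.01998 = 0.85, power 80.3%
- Two-tailed: (0.05 − 1.960×0.02003)/0.01998 = 0.54, power 70.5%

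The figure reproduces, but it concerns infections in the whole trial. Nothing comparable exists for weight change.

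**Assumed inputs.** Dutch children with two weights: N = 300 to 600, split equally. Infection risk: p = 17.5%, the midpoint of the protocol's two planning rates. Weight change is scaled per SD. Tests are two-sided.

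**Interaction, new infection (P≤0.10).** Approximate SE of the log ratio of odds ratios = √(4/(N·p·(1−p))). The true ratio is taken as 1.5 per SD, ln 1.5 = 0.405.

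| N | SE | 0.405/SE − 1.645 | Missed | 95% CI if the estimate were exactly 1 |
|---|---|---|---|---|
| 300 | 0.304 | −0.31 | 62% | 0.55 to 1.81 |
| 600 | 0.215 | 0.24 | 40% | 0.66 to 1.52 |

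A simulation of 1,000 trials per setting (odds ratio 1.5 per SD in the early arm, 1.0 in the late arm) gave power 0.36 at N=300 and 0.605 at N=600, that is, misses of 64% and 40%. The two methods agree.

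**Interaction, time to live PICU discharge (P≤0.10).** SE = √(4/events), assuming 95% have the event. The true ratio of hazard ratios is taken as 1.2, ln 1.2 = 0.182.

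- N=300: SE = √(4/285) = 0.118, missed in 54%
- N=600: SE = √(4/570) = 0.084, missed in 30%

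**Weight change by arm (P≤0.05).** In SDs of the change, the 95% half-width is 1.96×√(2/150) = 0.23 at N=300 and 1.96×√(2/300) = 0.16 at N=600. A true difference of 0.5 SD is missed in under 1%; a difference of 0.2 SD is missed in 59% and 31%.

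The SAP uses SD-score units, so the SD of the change matters. A true difference of 0.2 units is missed in:

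| SD of change | N=300 | N=600 |
|---|---|---|
| 0.5 | 7% | 0.2% |
| 0.75 | 36% | 10% |
| 1.0 | 59% | 31% |

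**Can a bounded claim be reached?**

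- *Weight change.* To place the 95% CI within ±m with 80% probability when the true difference is zero, n per arm = 2×(SD×(1.960+1.282)/m)². For an illustrative m of 0.2 units this gives 132 (SD 0.5), 296 (SD 0.75) and 526 (SD 1.0). With 150 to 300 per arm it is attainable if the SD is moderate.
- *Odds-ratio interaction.* A range of 0.67 to 1.5 needs a half-width below 0.405 on the log scale. The half-widths are 1.96×0.304 = 0.60 and 1.96×0.215 = 0.42, so the interval cannot fit at either size.
- *Hazard-ratio interaction.* A range of 0.8 to 1.25 needs a half-width below 0.223. It is 0.232 at N=300 (cannot fit) and 0.164 at N=600 (can fit).

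**The case against.** The strongest reply is that the harm is inferred. A reader might conclude that the SAP intends to report a non-significant result as confirmation. The documents do not say so. The two statements are introduced as expectations, and nothing prescribes how a null result will be worded. That stands, and the point is limited accordingly: the plan supplies no criterion by which these hypotheses could be supported.

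Two safeguards are also fairly cited. The Aims section makes the analysis of late PN, weight change and outcome in relation to undernourishment conditional on large enough groups. This shows that small numbers were foreseen, but no number is attached and the condition may cover only that split analysis. The 0.10 threshold makes a missed interaction less likely, but the miss rates above already use it, and it places no bound on effect size.

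A reader might further infer that the weight comparison itself is underpowered. The documents do not support that as a general statement. With 300 to 600 children a 0.5-SD difference would almost never be missed, and smaller differences depend on an SD that is not given. The gap there is the reading rule more than the sample.

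Finally, this is a secondary analysis of a completed trial, weight change is not among its listed primary or secondary outcomes, and the missing weights cannot be recovered. This limits the weight of the point and rules out a remedy that needs more data. It does not remove the need for a reading rule.

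**Conclusion.** The concern holds as a gap in inference. The SAP names two no-effect hypotheses for testing and offers only P≤0.05 and P≤0.10, in one centre's children, to judge them. Non-significance would support neither.

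The interaction is the more serious half. Under the assumptions above, a ratio of odds ratios of 1.5 per SD is missed in about 40% to 64% of trials. Even an estimate of exactly 1 would leave modification of roughly 1.5- to 1.8-fold within the 95% interval. For weight change the planned comparison may be quite informative, provided it is read through its interval.

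The Dutch N, the SD of weight change and the effect sizes are all assumed, so the percentages show scale only. That the tests cannot establish absence of effect does not depend on them. A correction to the SAP is worthwhile because it changes what may be concluded at little cost.

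**What to change.** In the SAP's Statistical analyses section:

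1. Report the late-minus-early difference in WFA/BFA SD-score change with a 95% CI. If the Mann-Whitney test is used, name an interval estimate to accompany it.
2. Name the arm-by-weight-change term, and report the ratio of odds ratios and the ratio of hazard ratios, each with a 95% CI.
3. State that a non-significant P will not be read as no difference, or as the relation being unaffected by late PN.
4. For weight change, allow a claim of no relevant difference only if the 95% CI lies within a margin in SD-score units that the sponsor fixes and justifies before analysis. A margin expressed in SDs of the observed change would not do: it is known only after analysis and is off the SAP's scale.
5. Label the interaction analysis exploratory and describe it by its CI, as inconclusive whenever the interval includes clinically relevant modification. Set no pass/fail range for it, since the working shows a plausible one may be unattainable.

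The cost is a few sentences. No new data are needed, and the estimates come from the planned analyses apart from the interval that would accompany a Mann-Whitney test. The sponsor must choose and defend a weight margin, and must accept that the interaction will probably be reported as inconclusive.
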